#### Exploratory procedures

##### Health economic evaluation

Participants may consent to provide access to data on use of healthcare services through MBS and PBS. These data provide detailed information on visits to healthcare providers, diagnostic tests and prescription medications including the amount paid out of pocket by participants and the amount paid by the Commonwealth government. Data will be extracted for the period 3 months prior to randomisation up until 8 months postrandomisation. The MBS/PBS data will be used to supplement self-report health service use obtained in a study-specific RUQ. The RUQ is adapted from previous Australian trials of mental health interventions and assesses the type, frequency and duration of health service use across diagnostic testing, medication use, outpatient, emergency and inpatient care. Questions also gather data on lost paid and unpaid work as well as an estimate of productivity while at work with symptoms (presenteeism).

##### Neuroimaging

Participants who provide optional consent to participate in the neuroimaging component of the study will be required to attend the MBCIU at The University of Melbourne (Parkville) for MRI scanning on two separate occasions. Treatment randomised, and treated waitlist control participants will complete their first scan (baseline) prior to their first treatment session and their second scan after their 16th session, or at Week 20. Prior to each visit, all participants will undergo an MRI safety screen by completing a safety questionnaire and review with radiographers at the MBCIU. By consenting to participate in the neuroimaging arm, participants also give consent for the research team to obtain relevant medical records and to share them with the MBCIU, if required for the purposes of the MRI safety screen. The entire MRI scan will take approximately 60 min, during which functional (fMRI) and structural images of their brain will be collected. While in the scanner, the Emotional Stroop Task will be administered. Participants will be presented with a series of words in different colours, appearing one at a time in quick succession on a screen. Participants will be required to identify the colour of each word as quickly and accurately as possible. Each word will be either a control word or a word related to DSCATT. Accuracy and reaction time will be collected on each trial. At the end of the MRI session, participants will be asked to rate each word on a number of dimensions (eg, emotional arousal, pleasantness/valence, relation to their physical or mental state) in a questionnaire facilitated by REDCap. Questionnaire data will aid the interpretation of task performance and neuroimaging findings.

The Emotional Stroop Task was chosen to investigate the neurobiological mechanisms underlying attentional bias toward information that has emotional relevance to the participant.^32^ Behaviourally, this bias is inferred when participants take longer (increased reaction time) to identify the ink colour of emotionally salient words compared with neutral (control) words. This effect, known as the ‘interference effect’, indicates that emotionally salient information can capture attention and divert cognitive resources away from the task at hand.^33^

We will use the Emotional Stroop task in the scanner to elicit brain activation in response to words describing participant’s symptoms or affective experience of DSCATT, then to compare this data between baseline and postintervention timepoints. We predict that our intervention will help participants shift attention away from symptoms and difficult illness-related thoughts/emotions to other aspects of their awareness. We therefore anticipate that the Emotional Stroop’s ‘interference effect’ will decrease after treatment, accompanied by changes in brain activation between timepoints.

### Outcomes

#### Feasibility outcomes

Table 1 outlines the outcome measures which will be used to assess the feasibility of the therapy for patients with DSCATT, of which retention rate will be the primary feasibility outcome.

#### Clinical, safety and exploratory outcomes

Table 2 outlines all clinical, safety and exploratory outcomes and timepoints where they will be assessed.

### Sample size

#### Sample size estimation

A total of 120 randomised participants is planned to provide adequate precision around the assumption of the primary feasibility outcome and to potentially inform the assumption of the pooled SD needed to work out the sample size of a future trial that is aimed to demonstrate the effect of the therapy. Assuming 120 participants are randomised, if study completion (ie, retention) is observed for 60% of these participants (72/120), then the two-sided 95% CI of the true underlying retention rate is (51%, 69%). The exact (Clopper-Pearson) method was used to obtain the 95% CI. For continuous (normally distributed) outcomes, a sample size of 70 in total (35 per treatment group) is considered sufficient to estimate the pooled SD with reasonable precision.^34^ Regarding the feedback interviews, sampling will continue until theoretical saturation is reached. A review of 100 studies analysing interview data demonstrated that 25 interviews were sufficient to achieve theoretical saturation.^35^ Thus, we anticipate that 25 participants who complete the therapy will be interviewed, and their transcripts analysed.

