## Study objectives

### Primary aim

Assess the feasibility of a 16-session ACT-informed treatment programme for adult patients with DSCATT. Markers of feasibility include practicality (including eligibility rate and treatment fidelity), acceptability (retention rate and satisfaction with treatment) and demand (including inquiry and participation rates). See table 1 for all feasibility markers used in the trial.

**Table 1 T1:** Feasibility outcomes

Area of focus	Feasibility research question/aims	Outcome measure and data source (quantitative or qualitative)	
		Quantitative	Qualitative
Acceptability	To what extent is the therapy judged as suitable, satisfying or attractive to participants with Debilitating Symptom Complexes Attributed to Ticks (DSCATT)?	Number of participants who do not withdraw prematurely from the programme (retention rate*) Treatment satisfaction questionnaire (satisfaction rate)	Reasons for premature withdrawal (field notes kept by project coordinator and/or trial therapist; semi-structured participant feedback interview) Satisfaction with treatment explored in semi-structured, post-treatment feedback interview
	What is the ability of participants to engage with the programme?	Number of sessions attended by participants (attendance rates)	Explored in semi-structured, post-treatment feedback interview
Demand	To what extent is the therapy likely to be used by patients with DSCATT (ie, how much demand is likely to exist?)	Number of people who express interest in the study (inquiry rate) Number of people who consent to participate in the therapy (participation rate)	Reasons for declining to proceed with the trial, obtained where possible (field notes kept by project coordinator)
Practicality	Is our screening process suitable to identify eligible candidates for randomisation into the trial?	Number of participants who are screened and deemed eligible for the trial (eligibility rate)	–
	Can the intervention be delivered as per a standardised therapist manual?	Therapist adherence to the intervention (treatment fidelity)	–
	Is it feasible to collect health service use via participant self-report and Medicare Benefits Scheme/Pharmaceutical Benefits Scheme (MBS/PBS) data access?	Completion rates of the self-report resource use questionnaire (RUQ) Number of participants who consent to MBS/PBS data access	–

* Primary outcome; measures adapted from Refs.^39^,^41^

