## Methods and analysis

### Trial design

A 32-week, individually randomised, waitlist-controlled, parallel convergent mixed-methods feasibility and pilot trial involving adults (≥18 years) located in Australia with DSCATT. This study will collect quantitative and qualitative data to address its study aims.

Participants will be randomly assigned in a 1:1 ratio to receive 16 sessions of ACT-informed therapy, delivered one-to-one by a trial therapist within a 20-week period and adjunctive to their pre-existing healthcare with follow-up at 32 weeks OR participants will be assigned to the waitlist control group where they will continue their treatment as usual for 32 weeks. After control participants complete the 32-week waitlist, they will be offered access to the 16-session therapy with a trial clinician.

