#### Study questionnaires

Participants will be sent a suite of questionnaires via REDCap at baseline (prior to randomisation into the therapy/waitlist control arm); and 10 weeks, 20 weeks (primary endpoint) and 32 weeks (follow-up) after randomisation (and irrespective of which session number the participant has completed in the treatment programme). These questionnaires will assess quality of life, general functioning, disability and impairment, physical symptoms, views about illness and healthcare utilisation (refer to the Outcomes section for further details). All participants who partake in the treatment programme (randomised participants and waitlist controls) will be provided with a treatment satisfaction questionnaire and the 20-item Negative Effects Questionnaire (NEQ)^28^ 20 weeks after commencing the therapy to ascertain its acceptability and safety.

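### The primary outcome is defined as retention in the therapy programme, but its planned precision is for study completion in both arms pooled; the stated interval is too narrow for programme retention in the therapy arm

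*Protocol article*

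**What the plan says.** The Feasibility outcomes paragraph under Outcomes refers to the measures in Table 1, "of which retention rate will be the primary feasibility outcome". Table 1, under Primary aim, describes that measure as "Number of participants who do not withdraw prematurely from the programme (retention rate") and places it in the Acceptability block, against the question "To what extent is the therapy judged as suitable, satisfying or attractive to participants". The programme is named in the opening sentence of the same section: "Assess the feasibility of a 16-session ACT-informed treatment programme for adult patients with DSCATT".

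The Sample size estimation section describes retention differently: "Assuming 120 participants are randomised, if study completion (ie, retention) is observed for 60% of these participants (72/120"). The interval it attaches to that rate runs from 51% to 69%. Here retention is equated with completing the study, and the denominator is everyone randomised.

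Trial design sets 1:1 allocation and says that "participants will be assigned to the waitlist control group where they will continue their treatment as usual for 32 weeks". The Waitlist control arm section adds questionnaires, telephone reviews of adverse events at Weeks 10 and 20, and an optional offer of the therapy after the Week 32 questionnaires. Treated waitlist outcomes assigns the data of those who accept to a separate observational analysis.

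**The concern.** The two sections describe different quantities. One is the proportion of people in the therapy programme who stay in it. The other is the proportion of all randomised people who finish the study. They differ in the event counted and in the denominator, and nothing in the article reconciles them.

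During the randomised phase, waitlist participants cannot leave a programme that they have not been offered. Their staying in the study answers a question about willingness to wait and to return questionnaires, and is at best indirect evidence on whether the therapy is acceptable.

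This is the trial's primary outcome, and the Power calculations section says that the sample size rests on precision rather than power. If the reported result follows the sample size section, it will not be the measure that Table 1 promises. If it follows Table 1, it will be less precise than planned.

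**Working it through.** **Inputs**
- Total randomised 120, assumed retention 60% (72/120), two-sided 95% exact (Clopper-Pearson) interval: Sample size estimation.
- Allocation 1:1, hence about 120/2 = 60 per arm: Trial design.
- Therapy-arm retention set to the same 60%, hence 0.60 × 60 = 36: an assumption, made so that only the denominator changes.

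**Formula.** For x retained out of n, the lower limit is the 2.5% quantile of Beta(x, n − x + 1) and the upper limit is the 97.5% quantile of Beta(x + 1, n − x).

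**Step 1: the plan's own figure.** x = 72, n = 120. The lower limit from Beta(72, 49) is 50.7% and the upper limit from Beta(73, 48) is 68.8%. These round to the stated 51% and 69%, so the arithmetic is right for that numerator and denominator. Width 18.2 points, half-width 9.1.

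**Step 2: Table 1's outcome in the therapy arm.** x = 36, n = 60. The lower limit from Beta(36, 25) is 46.5% and the upper limit from Beta(37, 24) is 72.4%. Width 25.9 points, half-width 13.0. The ratio of widths is 25.9/18.2, about 1.4.

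**Step 3: what a pooled 72/120 says about each arm.** It does not determine the therapy-arm rate. Two illustrative splits, neither of them a forecast, give the same pooled 60% (51% to 69%):

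| Therapy arm | Exact 95% CI, therapy arm | Waitlist arm |
|---|---|---|
| 30/60 = 50% | 36.8% to 63.2% | 42/60 = 70% |
| 42/60 = 70% | 56.8% to 81.2% | 30/60 = 50% |

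**Step 4: would later therapy for waitlist participants restore the denominator of 120?** The article gives no uptake figure, so uptake is varied as an assumption, with 60% programme retention throughout:

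| Waitlist uptake | Retained / in programme | Exact 95% CI |
|---|---|---|
| 0% | 36/60 | 46.5% to 72.4% |
| 25% | 45/75 | 48.0% to 71.1% |
| 50% | 54/90 | 49.1% to 70.2% |
| 75% | 63/105 | 50.0% to 69.4% |
| 100% | 72/120 | 50.7% to 68.8% |

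The stated interval returns only if all 60 waitlist participants take up the therapy. If the plan's 60% completion held in the waitlist arm, at most 0.60 × 60 = 36 would complete the study and be offered it, and the programme denominator could not exceed 60 + 36 = 96.

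**The case against.** The strongest reply is that study completion is a legitimate target for a feasibility trial. The abstract speaks of assessing the feasibility of a randomised, waitlist-controlled trial, and the article looks ahead to a larger one. On that reading the denominator of 120 and the interval are both correct. This stands: a reader might infer that the interval is simply wrong, and it is not. But the reading then conflicts with Table 1, both in its wording and in the acceptability question that it is meant to answer, so one of the two sections still has to change.

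Second, waitlist participants may receive the same 16 sessions later, and those who do also complete the satisfaction questionnaire and are invited to interview. This also stands: it would be too strong to say that half the sample never enters the programme, or that questionnaires are all that the waitlist involves. It does not rescue the stated precision, because uptake is optional, its size is not given, and the data go to a separate analysis.

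Third, the article does not say that retention will be reported only as a pooled figure. It fixes the interval method and leaves detail to an analysis plan not shown here. Attendance and reasons for withdrawal are also reported, so heavy loss from therapy would probably show elsewhere. The masking in Step 3 is therefore a possibility that the plan leaves open, not something that it commits to.

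Fourth, the sample size has a second justification, estimation of a pooled SD with 35 per group, which 60 per group exceeds before attrition. That part is unaffected.

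**Conclusion.** The definition and the planned precision of the primary outcome do not match, and the article needs correcting. For retention as Table 1 defines it, measured in the therapy arm, the planned precision at 60% is about 47% to 72%, not 51% to 69%: a half-width of 13 rather than 9 points. This rests on equal arms of 60 and on the plan's own 60% applying to the therapy arm. For study completion in both arms pooled, the stated interval is correct.

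Two stronger conclusions are not supported. A reader might infer a contradiction between Week 20 and Week 32, because Study questionnaires lists "20 weeks (primary endpoint) and 32 weeks (follow-up) after randomisation". That label belongs to the questionnaire visits. No section ties retention to Week 20, and the sample size section gives no week for completion, so what can be said is that the time point for retention is not stated. A reader might also infer that the wider interval fails some standard because it includes 50%. The article sets no retention threshold, and whether it should is a separate matter.

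**What to change.** State one definition, one denominator and one time point for retention, and use them in Table 1, the Outcomes section and the sample size section alike.

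- **To match Table 1 and the primary aim:** define the primary outcome as the proportion of participants randomised to therapy who do not leave the 16-session programme early, with a denominator of about 60. Restate the planned precision as 60% (36/60), exact 95% CI 47% to 72%. Report study completion by arm as a separate outcome.
- **If study completion is what is intended:** reword the Table 1 entry, reconsider its place under acceptability of the therapy, and report it by arm. The 51% to 69% interval may then stand for the pooled figure.

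The first option costs a less favourable stated precision, plus or minus 13 points instead of 9. Both are wording changes in the protocol and analysis plan, and neither needs extra participants.

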#### Power calculations

The trial is a pilot and feasibility study and is not designed to detect a treatment effect. As a result, the sample size justification is precision-based and no power calculation was performed.^34^

### Randomisation

A permuted block randomisation technique, stratified by sex at birth (female/male) will be used and accessed only by the project coordinator, who is unblinded during the trial.

#### Allocation concealment mechanism

The randomisation schedule will be computer-generated by a third-party statistician at the Methods and Implementation Support for Clinical and Health (University of Melbourne), not involved in the trial, including its design nor planned analyses. The schedule will be uploaded into the REDCap randomisation module^36^ by the project coordinator. The randomisation schedule and group assignment instruments will be hidden from the trial statisticians in the study’s REDCap project.

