#### Recruitment

Recruitment is anticipated to occur from June 2023 until October 2025. The trial will be advertised via a patient advocacy and tick-borne illness education organisation, the Karl McManus Foundation, who will circulate Human Research Ethics Committee (HREC)-approved recruitment flyers to their members. Clinicians and researchers known to work with DSCATT patients may also distribute these flyers to suitable candidates with a study invitation letter, if desired. In addition, the trial website will be listed on the Australian Government Department of Health’s tick bite associated illness in Australia website. If required, we will engage a clinical trial recruitment agency to obtain suitable candidates.

Study staff will respond to inquiries and address queries where applicable (via telephone/email, as preferred by the person inquiring). Candidates interested in participating in the study will be briefly telephone screened by the project coordinator to ascertain their age, diagnosed medical conditions, current symptoms and treatments. They will be sent the participant information and consent form (PICF) via email/post (as they prefer) and be asked to review in their own time. A suitable time to follow-up with the candidate will be arranged to address any further queries, and to book in their medical screening appointment if they wish to proceed with the trial.

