#### Consent

Written, informed consent will be required for study participation, and prior to completing the medical screening appointment to assess eligibility. PICFs will be issued to study candidates by the project coordinator via email/post, as preferred (see online supplemental material ‘PICF Master FIND trial V.3.3’). After reviewing the PICF, candidates may have as much time as desired while recruitment for the trial is open to consider participating. Informed consent procedures may be completed by the project coordinator or the trial physician. Participants will have the option to consent via one of three ways: (1) Face-to-face with study staff, (2) E-consent via Research Electronic Data Capture (REDCap),^24 25^ (3) Informed consent completed via telehealth/telephone, and a signed hard copy of the consent form returned via post or scanned and emailed to study staff. All consent forms will be co-signed by study staff who completed informed consent with the participant, and a copy of the dually signed consent form will be sent to the participant.

Participants may be asked to re-consent to the study if terms of consent change. For example, if study procedures are amended during the trial which affects how participant data is used, participants will be contacted to discuss this change and be asked to sign an updated PICF, if willing.

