#### Implementation

After satisfaction of inclusion criteria and completion of baseline questionnaires, participants will be randomised at a 1:1 ratio to the treatment intervention or waitlist-control arm, adjunctive to their treatment as usual. Randomisation will be completed by the project coordinator using the REDCap randomisation module.

The project coordinator will inform the participant of their group allocation following randomisation and determine their availability to commence sessions if allocated to the therapy arm. The participant will be assigned to a therapist based on matching availability. Participants randomised into the waitlist control group will be reminded of the trial timeline and opportunity to access therapy after 32 weeks.

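### The project coordinator, who takes part in enrolment, also uploads the randomisation schedule and has sole access to it, so the stated mechanism does not conceal allocation from everyone who enrols

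*Protocol article*

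**What the plan says.** All references are to the Protocol article.

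- **Generation** (Allocation concealment mechanism): "The randomisation schedule will be computer-generated by a third-party statistician", who is described as having no part in the trial.
- **Upload** (same section): "The schedule will be uploaded into the REDCap randomisation module^36^ by the project coordinator".
- **Access** (Randomisation): permuted blocks stratified by sex at birth, "will be used and accessed only by the project coordinator, who is unblinded during the trial".
- **Who is kept from the list** (Allocation concealment mechanism): "The randomisation schedule and group assignment instruments will be hidden from the trial statisticians in the study’s REDCap project".
- **Pre-screening** (Recruitment): interested candidates are "briefly telephone screened by the project coordinator".
- **Consent** (Consent): the coordinator issues the information and consent forms, and "Informed consent procedures may be completed by the project coordinator or the trial physician".
- **Eligibility** (Screening): a physician reviews the history, confirms the case definition and checks the remaining criteria.
- **Randomisation** (Implementation): "Randomisation will be completed by the project coordinator using the REDCap randomisation module". It follows satisfaction of the inclusion criteria and completion of the baseline questionnaires. The coordinator then informs the participant of the group.

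**The concern.** Allocation concealment means that those who bring participants into the trial cannot know the next assignment. Independent generation achieves this only if the list stays out of enrolling hands. Here the list passes at the next step to someone who handles candidates before randomisation and then randomises them. The one group from whom the concealment section expressly hides the list, the trial statisticians, have no stated enrolment role. Hiding it from them serves blinded analysis, not concealment.

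The safeguard matters in this trial. Participants and therapists are unblinded, Table 2 describes its measures as self-report unless otherwise specified, and the clinician-rated scale is completed by the participant's own therapist. The arms also differ in appeal: therapy now, or a 32-week wait. The coordinator works out when a participant allocated to therapy can start, and therapists are assigned by matching availability, so there is a practical motive to time a randomisation even without ill intent.

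The article plans treatment effect estimates with 95% CIs, an adverse event comparison and incremental cost-effectiveness ratios. All of these assume that the arms were formed without foreknowledge.

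**Working it through.** The point is procedural, so the main check sets the sections side by side.

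**1. Who can know the next assignment, and who enrols?**
- Third-party statistician: knows the list; no enrolment role.
- Project coordinator: uploads the list and has sole stated access; pre-screens, issues consent forms, may consent, randomises, announces.
- Trial physician: no stated access; confirms eligibility and may consent.
- Trial therapists: no stated access; no stated enrolment role.
- Trial statisticians: list hidden; no stated enrolment role.

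Only the coordinator has both access and an enrolment role. The Recruitment section attributes replies to inquiries to study staff in general and does not name who books the medical screening. The coordinator is the natural reading for the booking, since the pre-screening call leads into it, but the pre-screen, consent and randomisation roles are enough for the point.

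**2. Is a barrier described?** The article mentions no encryption of the file, no loss of access after upload and no other uploader. The Randomisation section could mean access to the randomisation procedure rather than to the list. Uploading a list still means handling it.

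**3. How much would a locked list gain?** Someone who holds the list can know every upcoming assignment, up to 120 of 120. Someone without it who sees past allocations can guess the arm with more places left in the current block. The article states no block size, so the sizes below are assumptions, and the guesser is assumed to know the block size.

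For blocks of 4 at 1:1, the chance of a correct guess at each position is:
- first: 1/2
- second: 2/3
- third: (2/3)(1/2) + (1/3)(1) = 2/3
- fourth: 1

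The average is (1/2 + 2/3 + 2/3 + 1)/4 = 2.833/4 = 70.8%. Full enumeration gives:

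| Assumed block size | Average correct guesses |
|---|---|
| 2 | 75.0% |
| 4 | 70.8% |
| 6 | 68.3% |
| 8 | 66.6% |

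The coordinator is unblinded and announces each allocation, so these figures, not 50%, are the comparator if block size becomes known.

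**4. Which estimates are exposed?** The plan's one sample-size figure is pooled retention. For 72/120, the Clopper-Pearson limits are the 2.5% quantile of Beta(72, 49) and the 97.5% quantile of Beta(73, 48). These are 50.7% and 68.8%, which reproduces the stated 51% to 69%.

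Pooled retention is (retained on therapy + retained on waitlist)/120. If a person's chance of staying is the same in either arm, exchanging two people between arms leaves that sum unchanged. It moves only if foreknowledge alters who enters, or if the chance of staying depends on the arm received. Between-arm estimates have no such protection: any systematic sorting of people into arms goes directly into the difference.

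**The case against.** The strongest reply has four parts.

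- **The eligibility decision is protected.** A physician without stated access confirms eligibility and may take consent. This stands. A reader might infer from the concealment section that the list is hidden from the statisticians alone, or that the coordinator decides who is eligible. The article supports neither: access is restricted to the coordinator, and the coordinator's screening is a brief telephone call.
- **Timing is not the coordinator's to decide.** Randomisation follows confirmed eligibility and completed baseline questionnaires, and candidates may take their time over consent. This stands in part. No section gives the coordinator control of timing. That the coordinator could influence it is an inference from performing the randomisation and being in contact with candidates beforehand.
- **The harm may be small.** The trial is not designed to detect a treatment effect, clinical reporting is mostly descriptive, and the primary outcome's precision rests on a pooled proportion. A reader might infer that retention would be biased. The document supports only that it could be, and less directly than the between-arm estimates.
- **User rights are operational detail.** A condensed article may leave these to the full protocol, and nothing here says that the coordinator inspects the list or knows the block sizes. If a lock-out exists, a sentence saying so would largely settle the matter. But the article does state its mechanism, and that mechanism puts the list in the hands of someone who enrols. This is a stated rule to correct, not an omission.

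A reader might also set full foreknowledge against a 50% guess. That overstates the gain, because this coordinator sees every past allocation in a permuted-block design.

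**Conclusion.** The point holds. As written, the mechanism exposes the schedule to a person who takes part in enrolment, and nothing in the article removes that exposure. Foreknowledge could affect who proceeds and when they are randomised. The threat is mainly to the between-arm clinical, adverse event and cost-effectiveness estimates, and secondarily to pooled retention.

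Neither the existence nor the size of any bias can be derived from the document. Foreknowledge of up to 120 of 120 assignments is a ceiling, and it assumes that the list is kept or remains viewable. A locked list would bring this down to partial predictability, 66.6% to 75.0% under the assumed block sizes if block size is known. The stated sample size and its confidence interval do not change.

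**What to change.** - Have the third-party statistician, or a REDCap administrator with no participant contact, upload and lock the schedule.
- Give the coordinator the right to randomise, without set-up or table-view rights, and do not disclose block sizes to the coordinator.
- Reword the Randomisation and Allocation concealment mechanism sections to state who uploads the list, who can view it, and that nobody who enrols can do so. If access is already restricted in this way, the rewording is all that is needed.
- If the coordinator has already handled the list, changing user rights does not undo that knowledge. Regenerate the unused part, report the process used to date, and show baseline characteristics by arm before and after the change.

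**Cost.** Before recruitment this is one upload by someone else, a change of user rights and a few sentences. During recruitment, add a new schedule for the remaining participants and a possible small imbalance where blocks are left incomplete (at most half a block per sex stratum). Recruitment was planned for June 2023 to October 2025, so if it has closed, what remains is to disclose the process and report baseline characteristics by arm. No outcome, sample size or clinical procedure is affected.
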